### Randomization: sequence generation, allocation concealment mechanism and implementation

The randomization will be 1:1 for each arm without stratification. Treatment allocation will be performed according to predefined block randomization list with random block sizes between four and ten. Only the data manager (UB) has access to this computer generated randomization list. Two to three days before surgery the data manager will prepare a computer generated study medication request form based on the patient’s study number. The request contains the patient’s name and the treatment allocation. The form will be placed in an opaque, sealed and signed envelope and will be directly delivered to the pharmacy by study personnel. Study medication will be prepared according to the request form by the hospital pharmacy as described earlier and will be delivered to the anesthesiologist by an assigned surgical resident.

If the allocated study treatment planned cannot be performed, the patient will remain on the study and will be included in the intention-to-treat (ITT) analysis. An explanation for the non-adherence must be supplied.

In case of an emergency two principal investigators (TC, IT) and the data manager can break the blinding of single patients. Unblinding is computer-based and is only available if the principal investigators are signed-in as users. Before unblinding a reason for unblinding has to be given. For each unblinding, the reason, the requestor, the computer ID, the time and date are recorded. The data manager will be automatically informed in case of an unblinding.

### Statistical analysis

The statistical analysis will be performed with SAS 9.1 (SAS Institute Inc., Cary, NC, USA). Missing values will be replaced with the last available value (the last observation carried forward approach, LOCF). For the baseline characteristics, descriptive statistics will be used as appropriate.

Two analyses (interims analysis and final analysis) will be performed for the primary outcome. To maintain the alpha, an O’Brien-Flemming alpha spending function [40] will be used. The alpha values used for the primary outcome will be 0.0039 in the interim analysis and 0.0488 in the final analysis. Both alphas will be adjusted for the exact proportion of information included in the interim analysis if the analysis is not performed for exactly 70 patients. For all other analyses, two-sided significance tests with an alpha of 0.05 will be applied.

All confirmatory analyses will be performed primarily as ITT analyses; the available data from all the patients will be assessed for the outcomes according to the randomization. To assess the treatment effects of dexamethasone vs. placebo in patients with no postoperative use of opioids, additional analyses will be conducted excluding the patients with protocol violations.

For the superiority analysis of dexamethasone vs. placebo in terms of the incidence of PONV (the primary outcome), a chi-square statistic will be applied. Mixed models assessing the mean ranks of the scores with adjustments for time and treatment vs. time interactions will be applied to analyze the following secondary outcomes: the severity of PONV, the intensity of pain at rest and the intensity of pain under provocation. The Mann–Whitney U statistic will be used to assess the following secondary outcomes: the required amount of anesthetic medication, the amount and type of postoperatively administered analgesics and the length of hospital stay. Postoperative morbidity and wound healing at the time of discharge and six weeks after the intervention will be assessed using a chi-square statistic.

Auxiliary, non-confirmatory analyses will be performed to assess the influences of baseline and treatment characteristics on the primary and secondary outcomes.

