### Setting and data collection locations

The patients will be enrolled at the outpatient Clinic of Endocrine Surgery. The participants will be enrolled only by the head of the Clinic of Endocrine Surgery (TC) or under his direct supervision. For each randomized patient, a case report form (CRF) will be generated and updated continuously throughout the hospitalization period. CRFs specifically created for this trial will be used for documentation. All the CRFs are Microsoft Excel-based, and the data will be entered electronically. The CRFs contain extensive probability and range checks to reduce erroneous entries, they are designed to reduce free-text entries to the minimum necessary, and selection from predefined lists (drop-down menus) will be the preferred means of data entry. The completed forms will be printed and signed by the entering physician and then sent to the trial coordinator, along with the data files. The six-week follow-up visits will occur at the outpatient Clinic of Endocrine Surgery.

Several procedures have been designed to enhance the quality of the trial conduct: reviews of the protocol and forms, the direct entry of the data into Excel data entry forms whenever possible, the automatic performance of consistency checks by the electronic data forms, the entry of written or printed data into electronic forms and a review of the data by the trial chair or a delegated person (with the medical content of all the forms reviewed and approved by a monitor).

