### Outcome measurements

The primary outcome will be the incidence of PONV, which will be assessed at postoperative hours 4, 8, 16, 24, 32 and 48. A patient will be considered to suffer from PONV if nausea or vomiting is documented at any of the postoperative assessments.

One secondary outcome will be the severity of the PONV, measured with a score ranging from 0 to 3 (0 for no nausea; 1 for mild nausea, defined as nausea requiring a single administration of an antiemetic drug; 2 for severe nausea, defined as nausea requiring the repeated administration of antiemetic drugs; and 3 for nausea leading to vomiting).

Other secondary outcomes will be the intensity of pain at rest and under provocation (while rotating the neck 90° to each side), measured at postoperative hours 4, 8, 16, 24, 32 and 48 with a Verbal Rating Scale (VRS) ranging from 0 to 10, with 0 considered to be no pain and 10 considered to be the worst pain imaginable. Additional secondary outcomes will include the length of hospital stay (measured as the number of hours after the intervention), wound healing at the time of discharge and six weeks after the intervention, the amount of anesthetic medication required (total amount of administered fentanyl, remifentanil, rocuronium measured in mg and the total amount of administered remifentanil measured in μg) and postoperative in-hospital morbidity, including wound infection, reoperation, bleeding, prolonged intubation, laryngeal nerve lesion, urinary retention, urinary tract infection, pulmonary infection and gastrointestinal hemorrhage or newly occurring insulin dependence in diabetic patients.

For the safety analysis, adverse events (AEs) and serious adverse events (SAEs) will be evaluated. The patients will be instructed by the investigator to report the occurrence of any AE, defined as an unfavorable and unintended sign, symptom or disease temporally associated with the treatment provided in the present trial. The investigator (treating physician) will be asked to verify the absence or presence of all the AEs predefined on the CRF. Information in the patients’ medical files will be reported using the Common Terminology Criteria for Adverse Events v4.03 (CTCAE 4.03) coding system, rather than a narrative description. AEs will be scored as grade 1 (a mild AE) to grade 5 (death related to the AE), and a causality assessment will be performed.

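### LOCF is prescribed without limit: it puts early scores into the later time points of the pain and severity models, and the primary endpoint has no considered rule for event-free patients with missed assessments

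*Protocol article*

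**What the plan says.** The Statistical analysis section gives one missing-data rule for the whole analysis: "Missing values will be replaced with the last available value", named there as LOCF. It restricts the rule to no outcome and gives no fallback for a patient without an earlier value.

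The outcomes it meets are these:

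- **Primary outcome.** PONV incidence, "which will be assessed at postoperative hours 4, 8, 16, 24, 32 and 48". Under Outcome measurements, "A patient will be considered to suffer from PONV if nausea or vomiting is documented at any of the postoperative assessments". For the comparison of arms, "a chi-square statistic will be applied".
- **Severity of PONV, pain at rest, pain under provocation.** "Mixed models assessing the mean ranks of the scores with adjustments for time and treatment vs. time interactions will be applied" to these three.
- **Wound healing.** Assessed at discharge and at six weeks, each by chi-square.

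The same section describes the intention-to-treat analysis as one in which "the available data from all the patients will be assessed for the outcomes according to the randomization". Under Setting and data collection locations, the case report form is "updated continuously throughout the hospitalization period", with a six-week outpatient visit afterwards. Under Ethical issues, patients may withdraw and their data up to that point are kept.

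**The concern.** **Repeated measures.** Pain and nausea normally ease over the first two days. Carrying a 16 h or 24 h score to 48 h assigns a patient a level typical of an earlier time. If one arm has more gaps than the other, its late means are pulled further towards early values, and the treatment-by-time term absorbs the artefact. The filled-in values are also treated as measurements, so the model credits itself with information it lacks. None of this is needed: a mixed model can be fitted to whichever assessments exist, approximately valid under missing at random (approximately, because the models are on ranks).

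**Primary endpoint.** The rule looks like neutral imputation but amounts to assuming that nothing happened at missed assessments. An event-free patient last seen at 16 h is counted exactly like one followed event-free to 48 h. That lowers the counted incidence, and it can distort the comparison if such patients are not spread alike over the arms.

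**Wound healing.** Read literally, the rule gives a patient who misses the six-week visit the wound status recorded at discharge, although healing in that interval is what the visit is meant to capture.

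**Working it through.** The sample size does not depend on the missing-data rule, but it supplies the event rates used below. With 48% versus 24%, two-sided 0.05, power 0.80 and pooled variance, the unrounded total is 123.2; × 1.006 = 123.9, so 124; 124 / 0.82 = 151.2, so 152. The article's 123, 124 and 152 are reproduced. The 18% is a protocol-violation rate, not a missing-data rate.

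**1. What LOCF does to the any-time endpoint.** Six binary assessments and six missing/observed flags give 2^6 × 2^6 = 4096 combinations.

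- In the 64 with nothing observed, LOCF gives no value.
- In the other 4032, patient status under LOCF was compared with status when missing is scored as no event. They differ in 0.
- A gap after a documented episode is carried as PONV, but that patient is already a case.
- A gap at 4 h has nothing to carry, so LOCF is undefined there.

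**2. Consequence for incidence (assumed inputs).** Let d be the share of patients missing the late assessments and s the share of PONV cases whose only episode falls in the missed window, with d unrelated to PONV. Counted incidence = p(1 − d·s).

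*Equal missingness, planned effect, final alpha 0.0488:*

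| d, s | Placebo | Dexamethasone | Relative risk | Power, 62/arm | Power, 76/arm |
|---|---|---|---|---|---|
| none | 48.0% | 24.0% | 0.50 | 80.0% | 87.5% |
| 10%, 10% | 47.5% | 23.8% | 0.50 | 79.3% | 86.9% |
| 30%, 30% | 43.7% | 21.8% | 0.50 | 73.8% | 82.2% |

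*Unequal missingness, planned effect, s = 30%:* d = 10% placebo and 30% dexamethasone gives a relative risk of 0.469. The reverse gives 0.533, with power 67.3% at 62 per arm. The direction depends on which arm has more gaps.

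*No true effect (48% in both arms), 60% of dexamethasone and 30% of placebo patients discharged by 24 h and not assessed afterwards:*

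- s = 20%: 0.48(1 − 0.2 × 0.6) = 42.2% versus 0.48(1 − 0.2 × 0.3) = 45.1%, a false benefit of 2.9 points.
- s = 10%: 45.1% versus 46.6%, a false benefit of 1.4 points.
- At 76 per arm, normal approximation, the rejection rates are 6.3% and 5.2% against a nominal 4.88%.

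**3. Repeated measures (assumed example).** A 0–10 score has means 4, 3.6, 3, 2.4, 1.9 and 1.2 at the six times. There is no treatment effect, 76 patients per arm, and everything after 16 h is missing at random within arm for a share of patients. The expected LOCF shift at 48 h is the difference in missing shares times the fall from 16 h to 48 h: (0.30 − 0.10) × (3.0 − 1.2) = 0.36 points. Over 300 simulated trials:

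| Missing after 16 h | LOCF: difference at 48 h | LOCF: rejects | Observed data, likelihood: difference | Likelihood: rejects |
|---|---|---|---|---|
| 10% vs 30% | 0.34 | 27% | −0.02 | 7% |
| 20% vs 20% | 0.00 | 5.7% | −0.01 | 6.3% |

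The Monte Carlo standard error near 6% is √(0.06 × 0.94 / 300) = 1.4 points, so 5.7%, 6.3% and 7% are not distinguishable from 5%. The example uses raw scores, not ranks, and tests the 48 h difference, not the interaction. It shows the mechanism and does not predict this trial's result.

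**The case against.** Four objections deserve an answer.

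**The primary-endpoint result does not come from LOCF alone.** A case must be documented, so an undocumented episode is not a case whether or not values are carried forward. This stands: deleting the LOCF sentence by itself changes no patient's primary status. What remains is that neither the endpoint definition nor LOCF deals with an event-free patient whose assessments are incomplete, and LOCF gives the impression that this has been handled.

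**The article does not say that patients leave before 48 h.** This stands too. Because the case report form is kept up during the hospital stay, and length of stay is an outcome the trial hopes to change, a reader might infer that 32 h and 48 h values are lost at discharge, more often under dexamethasone, and that the primary test is therefore tilted in its favour. The documents do not support that. They schedule assessments to 48 h, give no discharge times, and do not say that assessment stops at discharge. The Background also says PONV prolongs stay, so the assumption that discharge is unrelated to PONV is itself doubtful.

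**The amounts are small.** Even the assumed 2.9 points compares with a planned difference of 24, and equal missingness leaves the relative risk at 0.50. This is right for the primary outcome. For the pain scores the distortion can be larger, but only with unequal missingness and falling scores.

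**Details may sit in an analysis plan that is not shown.** That would excuse silence. Here the article states a method, and it is that method which is questioned.

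A reader might also see a contradiction between LOCF and the reference to available data. There is none: that clause defines intention-to-treat as all patients analysed as randomized, and carrying forward an available value is compatible with it.

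**Conclusion.** The point holds in a limited form. It is firmest for the three repeated-measures outcomes: LOCF replaces unobserved late scores with early ones, although the models already planned can use incomplete records. With missingness equal in both arms, the worked example shows no between-arm bias at 48 h; with 10% versus 30% it gives a false difference of about a third of a point.

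For the primary endpoint, LOCF with the endpoint definition is the same as scoring incomplete event-free patients as no PONV. Equal missingness costs some incidence and power (80.0% falling to between 79.3% and 73.8% at 62 per arm, for d and s each from 10% to 30%). The comparison is biased only if missingness differs by arm or relates to outcome; 1.4 to 2.9 points is an illustration under one such assumption.

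No magnitude can be derived from the documents. If nearly all patients are assessed to 48 h, the effect is negligible, and so is any use for LOCF. The change should be made, but the point does not by itself put the primary conclusion in doubt.

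**What to change.** 1. Delete the LOCF sentence.
2. Fit the rank-based mixed models for PONV severity and both pain scores to observed assessments only, and state missing at random as the working assumption.
3. For the primary endpoint, count any patient with a documented episode as a case. For patients with no documented episode and one or more missed assessments, use multiple imputation within arm based on the earlier assessments. Report missing = PONV and missing = no PONV as sensitivity bounds.
4. Do not carry wound status at discharge forward to six weeks.

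Cost: a change of wording and a little programming, with no new data or patients. The Trial status section says recruitment is ongoing, so the change can be fixed before the final analysis.

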### Sample size calculation

A sample size determination was conducted for the main outcome variable, the incidence of PONV, using R environment version 13.2 with the gsDesign package. A preliminary retrospective analysis of 100 patients revealed a total incidence of PONV of 48% (unpublished data), confirming previous studies [39]. Based on a power of 0.80 (p = 0.05, two-sided) to detect a 50% reduction in the incidence in PONV (48% vs. 24%) as the clinically relevant treatment advantage between two balanced arms, a total of 123 patients were required for a fixed design. To account for deviations from the expected effect size and incidence due to the avoidance of opioids for postoperative pain relief, a group sequential design was implemented with one interim analysis after 70 patients have completed the study treatment. In a symmetric, two-sided group sequential design with an O’Brien-Flemming alpha spending function [40], the inflation factor was 1.006. The adjusted sample size was estimated to be a total of 124 patients (62 patients per arm). With an assumed rate of 18% protocol violations (derived from a preliminary retrospective analysis of 100 patients), the calculated total sample size was 152 patients (76 patients per arm). To recruit this number of patients, a 30-month inclusion period was anticipated.

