### Interim analysis

An interim analysis is planned to assess the primary outcome and the safety of the treatment after 70 patients. For the interim analysis, the data manager will provide the data to the trial statistician with coded treatment assignments (A, B). The statistician will provide summary tables of grade 3 and 4 SAEs and a blind analysis of the primary outcome. Based on these data, the trial chairperson and co-chairperson will decide whether to continue the trial without modifications, continue the trial with modifications or halt the trial due to safety or efficacy concerns. Only if the results are insufficient for that decision the treatment assignments will be revealed and the data will be analyzed again. Unless the benefit of the treatment is demonstrated “beyond a reasonable doubt” by the interim analysis, no formal discontinuation due to efficacy is foreseen. The decision about trial continuation will be based not only on the statistical results but also on clinical judgment [41]. The statistical boundary, requiring p < 0.0039 at the interim analysis to halt due to efficacy, will serve as a guide. The results of the interim analysis will be confidential and strictly limited to the trial statistician, trial chairperson and trial co-chairperson. To avoid bias in the subsequent trial, the results of the interim analysis will be treated confidentially and will not be communicated to the outside or to the clinical investigators involved in the trial.

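### The interim and final levels (0.0039 / 0.0488) and the inflation factor 1.006 come from O'Brien-Fleming spending with 0.05 in one tail, not from the declared symmetric two-sided 0.05 design; the effect on overall alpha is very small

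*Protocol article*

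**What the plan says.** Three sections of the protocol article bear on this point.

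- **Sample size calculation.** Power is 0.80 at two-sided 0.05 for 48% against 24%, and "a total of 123 patients were required for a fixed design". One interim look follows after 70 patients: "In a symmetric, two-sided group sequential design" with O'Brien-Fleming alpha spending, inflation factor 1.006. The size then becomes 124, and 152 after allowing for 18% protocol violations.
- **Interim analysis.** "The statistical boundary, requiring p < 0.0039 at the interim analysis to halt due to efficacy, will serve as a guide". The decision also rests on clinical judgment.
- **Statistical analysis.** "The alpha values used for the primary outcome will be 0.0039 in the interim analysis and 0.0488 in the final analysis". Both levels are to be readjusted to the actual information fraction, but only if the look does not fall at exactly 70 patients. The primary test is a chi-square test, and the intention-to-treat analysis is primary.

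Neither of the last two sections says whether the two levels are two-sided, and none of the three says whether the information fraction is 70/152 or 70/124.

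**The concern.** A symmetric two-sided design at 0.05 spends 0.025 in each tail. Boundaries computed that way at 70 patients should reproduce the printed levels and inflation factor, and they do not. These levels are the guide for an early efficacy stop and the criterion for the final primary claim, so they should follow from the declared design. If they come from a different error rate, the early threshold is not the one the design implies, and the two levels together need not hold 0.05. The readjustment rule does not repair this, because at the planned 70 patients the printed pair stands.

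**Working it through.** **Inputs.** Rates 48% and 24%, 1:1 allocation, power 0.80, two-sided 0.05, interim at 70, sizes 123, 124 and 152, 18% violations, inflation 1.006, levels 0.0039 and 0.0488. All are from the protocol. The fraction t is not stated, so both candidates are tried: 70/152 = 0.4605 and 70/124 = 0.5645.

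**Step 1: reproduce the sample size.** With the pooled variance under the null, the mean rate is 0.36 and the total is

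2 × [1.960 × √(2 × 0.36 × 0.64) + 0.8416 × √(0.48 × 0.52 + 0.24 × 0.76)]² / 0.24² = 123.2.

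This agrees with the stated 123. Then 123.2 × 1.006 = 123.9, giving 124, and 124 / 0.82 = 151.2, giving 152. With 1.645 in place of 1.960 (0.05 in one tail) the total would be 96.8, or 97. So the sample size rests on two-sided 0.05.

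**Step 2: interim level.** The O'Brien-Fleming-type spending function for error a in one tail is f(t) = 2 × [1 − Φ(z(1−a/2) / √t)].

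- a = 0.05, t = 0.4605: 1.960 / 0.6786 = 2.888, f = 0.003875. This is the printed 0.0039.
- a = 0.025, t = 0.4605: 2.2414 / 0.6786 = 3.303, f = 0.000957 per tail, or 0.0019 two-sided.
- a = 0.025, t = 0.5645: 2.2414 / 0.7513 = 2.983, f = 0.002853 per tail, or 0.0057 two-sided.

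**Step 3: final level and inflation.** The final boundary is solved from the joint normal distribution of the two test statistics, whose correlation is √t. Inflation is the squared ratio of the drift needed for 80% power to that of the fixed design.

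| Design | t | Interim | Final | Inflation |
|---|---|---|---|---|
| Printed | not stated | 0.0039 | 0.0488 | 1.006 |
| 0.05 in one tail | 70/152 | 0.0039 | 0.0488 | 1.0056 |
| 0.025 per tail (declared) | 70/152 | 0.0019 | 0.0494 | 1.0024 |
| 0.025 per tail (declared) | 70/124 | 0.0057 | 0.0482 | 1.0066 |
| 0.025 per tail | 0.5 | 0.0031 | 0.0490 | 1.0037 |
| Spending function applied to the total two-sided 0.05 | 70/152 | 0.0039 | 0.0484 | 1.0062 |
| Classical O'Brien-Fleming, two-sided | 70/152 | 0.0037 | 0.0485 | 1.0057 |

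Only 0.05 in one tail at 70/152 matches all three printed figures. Putting 0.05 in each of two tails gives the same three. The declared design reaches 0.0039 only at t of about 0.524, a fraction the protocol does not mention, and there the final level is 0.0487 and the inflation 1.005.

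**Step 4: consequence for alpha.** Applying 0.0039 and 0.0488 to two-sided p-values gives overall type I error 0.0504 at 70/152 and 0.0499 at 70/124. It equals 0.05 at t of about 0.537. If 0.0039 is kept at 70/152, the final level that holds 0.05 is 0.0484.

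**Step 5: consequence for the interim.** 0.0039 / 0.0019 is about 2.0 (z of 2.89 against 3.11). An exact binomial calculation with 35 per arm at 48% against 24% gives a 21.4% chance of crossing 0.0039 and 15.2% of crossing 0.0019.

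**Step 6: exact check of the chi-square test** (35 then 76 per arm, common rates from 24% to 48%). Type I error runs from 0.0456 to 0.0535 with the printed pair and from 0.0451 to 0.0526 with 0.0019/0.0494. The difference is below 0.001 at every rate tried. Power at 48% against 24% is 0.881 with either pair.

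**The case against.** The strongest reply is that little follows in practice, and most of it stands.

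- **0.0039 can be a valid two-sided interim level.** Spending the total two-sided 0.05 through the same function gives 0.0039 at 70/152. This stands, but the final level must then be 0.0484, so the printed pair still does not follow. The word symmetric also points to 0.025 per tail.
- **The direction depends on the information base.** On 124 patients 0.0039 is stricter than the declared design's 0.0057, and overall alpha is 0.0499. This stands as a limit on the alpha claim. But the printed figures do not come from 70/124, and the primary analysis includes all randomized patients.
- **The excess is negligible.** It is 0.0004 on the normal approximation, less than the variation due to the discreteness of the chi-square test. The corrected pair itself exceeds 0.05 at some rates. This stands.
- **The interim boundary is only a guide.** This also stands, so 21.4% and 15.2% are chances of crossing the threshold, not of stopping. It does not cover 0.0488, which is the criterion for the final analysis.

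A reader might also infer that the levels would be applied to one-sided p-values, so that the trial would run at two-sided 0.10. The document does not support this. It declares a two-sided design, and the ordinary p-value of the planned chi-square test is two-sided.

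**Conclusion.** The printed levels and inflation factor do not follow from the declared design. They reproduce only with 0.05 in one tail (or in each tail) at 70/152, whereas the 123-patient calculation uses two-sided 0.05. The guide threshold for early efficacy is about twice the declared design's value at that fraction, and overall alpha is about 0.0504, falling to 0.0499 on a base of 124. These sizes assume two-sided p-values, a look at exactly 70 patients and, unless stated otherwise, 152 as the base. The protocol does not say how the levels were obtained, so their origin is inferred from the three-figure match.

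Severity is low. A reader might take the doubled interim threshold as a material loss of error control, but the figures do not bear that out. The choice of pair decides the result only if the interim p-value lies between 0.0019 and 0.0039, or the final p-value between 0.0484 and 0.0494.

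**What to change.** Rerun the boundary calculation with 0.025 in each tail. State in the Statistical analysis section that both levels are two-sided, that information is intention-to-treat patients out of 152, and that both are recomputed from the actual fraction at the look. At 70/152 the levels become 0.0019 and 0.0494. If 0.0039 is to be kept as the interim level, lower the final level to 0.0484 instead.

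Bring the three sections into line: the inflation factor under Sample size calculation (1.002 for the pair 0.0019/0.0494), the guide threshold under Interim analysis, and the pair under Statistical analysis. The sample size does not change: 123.2 × 1.0024 = 123.5, giving 124, and 124 / 0.82 gives 152.

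The cost is one rerun of the boundary program and a few words in three sections, ideally before the interim data are seen. The 0.0019/0.0494 pair makes the interim guide stricter and the final level slightly more generous; the 0.0039/0.0484 pair leaves the guide alone and tightens the final level slightly.
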